#### Inclusion criteria

Children aged 6 to 11 years (1st to 5th grade at school) at baselineBoth Saudis and non-SaudisChildren for whom the person with parental responsibility has signed the consent form

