#### Primary outcome

The study primary outcome is the change in the number of teeth with untreated dental caries in both primary and permanent teeth over 12 months. The underlying assumption of the selected primary outcome is that students in the intervention group will visit a dentist during the trial period and as a result will have fewer untreated decayed teeth than those in the comparison group. While the use of a clinical outcome might be perceived more sensitive to services provided after referral, its use is deemed appropriate for this trial as the students will be referred to a specific institution with a system in place to handle those referred.

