#### Between-group comparisons

A comparison of demographic (sex, age), socioeconomic (family income, parental education) and behavioural characteristics (tooth-brushing frequency, dental attendance pattern, last dental visit, reason for last dental visit, use of fluoridated toothpaste and sugars intake) and caries levels in deciduous and permanent teeth between both intervention groups will be carried out using the chi-square test for categorical variables and a *t* test for continuous variables.

We will report absolute and relative measures of effect; that is, absolute and relative difference in means for continuous outcomes (change in number of teeth with untreated caries) and risk differences and relative risks for dichotomous outcomes (changes in the proportions of children having teeth with untreated caries and visiting the dentist). For the primary outcome (change in number of teeth with untreated caries), negative binomial regression will be used to estimate relative differences (incidence rate ratios) and predictive margins to estimate absolute differences between intervention groups. This analytical technique will allow accounting for stratification of the sample, clustering of children within schools and any baseline socioeconomic and behavioural differences between trial groups. For secondary outcomes, log-binomial regression will be used to estimate relative risks for the change in the proportions of children with untreated dental caries and who visited the dentist. Predictive margins will also be used to estimate absolute differences in each secondary outcome. Intention-to-treat analysis will be used to handle missing values in categorical outcomes. Multiple imputation will be considered as an option for continuous outcomes.

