#### Supplemental analysis

Subgroup analysis will be conducted to explore the effectiveness of school-based dental screening on primary and secondary outcomes among specific subgroups. To that end, we will compare outcomes between the two trial groups among children who were screened positive, and then, among those who reported being regular attenders at baseline.

Comparisons will also be reported stratified by area (high and low socioeconomic status) and dentition (number of teeth with untreated caries in primary or permanent teeth).

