The selected study design addresses some of the methodological limitations of previous studies [7, 8]. Data collection on participants’ socioeconomic and behavioural factors will help accounting for baseline differences between the two trial groups (if they are unbalanced after randomisation) that might impact use of dental services [21]. However, this study must be conducted with relatively limited resources as part of PhD project and will probably not answer all relevant questions on the effectiveness of school dental screening in Saudi Arabia. Future research should build upon what we are starting in this study, by looking into cost-effectiveness analysis and reasons behind any lack of effectiveness. A national study could also provide more information on effectiveness in different parts of the country.

Finally, it is worth noting that the education system in Saudi Arabia is segregated by children’s gender. Due to cultural restrictions, female dentists cannot access boys-only schools and vice versa. Although we have recruited and trained separate teams for accessing boys- and girls-only schools, access to both types of schools are heavily dependent on approval from the Ministry of Health as the principal investigator, who will oversee the entire fieldwork, is female. This might result in a male-to-female ratio different to 1-to-1.

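### Age is not named among the baseline variables for adjustment; prespecifying it would cost nothing and would guard against a chance age difference between arms

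*Protocol article*

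**What the plan says.** The Between-group comparisons section of the protocol article sorts the baseline variables into categories before testing them between arms: "A comparison of demographic (sex, age), socioeconomic (family income, parental education) and behavioural characteristics". Age and sex form the demographic category. The same section then says of the primary model that "negative binomial regression will be used to estimate relative differences (incidence rate ratios) and predictive margins to estimate absolute differences", and that this technique permits "accounting for stratification of the sample, clustering of children within schools and any baseline socioeconomic and behavioural differences between trial groups". The demographic category does not appear in that list.

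The Discussion makes a second statement about adjustment, with the same two categories and a condition: "Data collection on participants’ socioeconomic and behavioural factors will help accounting for baseline differences between the two trial groups (if they are unbalanced after randomisation".

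Eligibility is "Children aged 6 to 11 years (1st to 5th grade at school", and the primary outcome is "the change in the number of teeth with untreated dental caries in both primary and permanent teeth over 12 months". The Randomisation section allocates schools by simple randomisation within area strata. The Supplemental analysis section adds reporting stratified by "dentition (number of teeth with untreated caries in primary or permanent teeth". No section names age or grade as a covariate.

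**The concern.** The outcome counts both dentitions together, in children spread over five school grades, across a full year. A decayed primary tooth that is shed leaves the count without any dental visit, and newly erupted permanent teeth can enter it. How often either happens should depend on age. The Primary outcome section reads a lower count as the consequence of visiting a dentist, so age-related change is variation that the analysis would do well to separate out. That age is prognostic is an inference from the age range and the pooled count; the article does not state it.

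Age is collected, fixed before allocation and free of treatment effect. If it predicts the outcome and is not in the model, some precision is lost. A chance difference in age between the arms then carries into the estimate. With 16 schools and stratification by area only, such a difference is not negligible. Tying adjustment to observed differences also leaves the choice of covariates until after the baseline data are seen.

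**Working it through.** **The plan's own figure.** The Justification of sample size section gives 455 per arm for a 0.50-tooth difference, 80% power, 5% significance (two-sided assumed), ICC 0.03 and 75 children per school. No SD is given. The design effect is 1 + (75 − 1) × 0.03 = 3.22. Solving n = 2 × (SD × (1.96 + 0.842) / 0.50)² × 3.22 = 455 for SD gives 1.50. As a check, SD 1.5 gives 141.3 × 3.22 = 454.9. The figure is consistent with an unstated SD of 1.5, and nothing below changes it.

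**Age spread (assumed).** With equal numbers in grades 1 to 5 and ages uniform within a grade, the variance is 2 + 1/12 = 2.083 and the SD is 1.44 years.

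**Chance difference in mean age between arms.** I assume 8 schools per arm (16 schools, 1:1) of 455/8 = 56.9 children each. Simple randomisation may give an unequal split, and the sample size paragraph speaks of six clusters per group, so 8 per arm is itself an assumption. For a school ICC of age ρ:

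SD of arm difference = 1.44 × √(2 × (1 + 55.9ρ) / 455)

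The shift in the estimate is the 95% limit (1.96 × SD) times the slope in teeth per year of age. The documents give neither ρ nor the slope, so ranges are shown.

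| ρ (assumed) | SD, years | 95% limit, years | Shift at slope 0.1 | Slope 0.2 | Slope 0.3 |
|---|---|---|---|---|---|
| 0 | 0.096 | 0.188 | 0.019 | 0.038 | 0.056 |
| 0.03 | 0.157 | 0.307 | 0.031 | 0.061 | 0.092 |
| 0.10 | 0.246 | 0.481 | 0.048 | 0.096 | 0.144 |

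The range at the 95% limits is 0.02 to 0.14 teeth, which is 0.019/0.50 = 4% to 0.144/0.50 = 29% of the target difference. A more ordinary case is one SD at ρ = 0.03: 0.157 years × 0.1 to 0.3 = 0.016 to 0.047 teeth, or 3 to 9% of the target.

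**Precision.** Suppose the grade mix is similar across schools, so that age explains only within-school variation. At ICC 0.03, the within-school part of the variance of an arm mean is 0.97/3.22 = 30% (75 per school) to 0.97/2.68 = 36% (57 per school). If age explains 3 to 10% of the within-school variance (assumed), the SE falls by:

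- low end: 1 − √(1 − 0.03 × 0.30) = 0.5%
- high end: 1 − √(1 − 0.10 × 0.36) = 1.8%

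The top of the shift range and this small SE gain are different scenarios. The first lets mean age vary between schools (ρ = 0.10); the second does not.

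**The case against.** The strongest reply is that the adjustment sentence describes what the model is able to do. It is not a closed covariate list, it does not exclude age, and a full list may sit in an analysis plan that is not shown. This stands as far as it goes: it would be too strong to say that the plan rules age out. But the article describes its adjustment twice, by category, and on neither occasion includes the category in which it has placed age.

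Second, a reader might infer that an age difference biases the result. The documents do not support that. Schools are randomised within strata, so a chance age difference has expectation zero. It adds variance and can move one trial's estimate. Bias would need recruitment or loss that differs by age and by arm, and nothing in the article shows this. Nor does an age difference between schools matter in itself; only a difference between arms does. Every school contributes the same grades, and teams stay a week working through the classrooms, which limits imbalance. The grade mix among consenting children is still not fixed.

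Third, a reader might infer a large gain in precision. If age explained 20% of the variance at both child and school level, the SE would fall by 11%. The documents give no age-outcome association, and a gain of that size would need age to account for between-school variation as well, which they do not show.

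Fourth, the dentition-specific results would help show whether a pooled finding is driven by primary teeth. They are supplemental, however, and do not adjust the primary comparison. Finally, a randomised comparison without age is valid. That is correct, and it is why this is an improvement and not a defect.

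**Conclusion.** The point holds in a limited form. As stated, the adjustment covers socioeconomic and behavioural differences, conditional on imbalance, and does not name age, which is a likely predictor of a pooled tooth count in children of 6 to 11 years. The consequence is avoidable random error. At the 95% limits of chance imbalance it could move the estimate by about 0.02 to 0.14 teeth against a 0.50-tooth target; the upper end needs the steepest slope and the highest age ICC together. The routine precision gain is small, about 0.5 to 2% in SE if age varies only within schools, so the main value is protection against arm imbalance. All of these sizes rest on assumed slopes, age ICCs, explained variance and an 8-versus-8 split of schools. The case for naming age does not depend on any particular value. It is a free improvement.

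**What to change.** In Between-group comparisons, add a sentence naming child age at baseline (or school grade) as a prespecified covariate in the primary negative binomial model and in the log-binomial models for both secondary outcomes, included whatever the baseline table shows. An age-by-baseline-count term is not needed; it could be kept as an optional sensitivity analysis.

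The cost is one sentence and, for a linear age term, one child-level degree of freedom per model (four if grade is entered as categories). No new data are required, since age is an entry criterion and is already on the parental questionnaire. The sentence should be fixed before follow-up outcomes are seen.

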#### Supplemental analysis

Subgroup analysis will be conducted to explore the effectiveness of school-based dental screening on primary and secondary outcomes among specific subgroups. To that end, we will compare outcomes between the two trial groups among children who were screened positive, and then, among those who reported being regular attenders at baseline.

Comparisons will also be reported stratified by area (high and low socioeconomic status) and dentition (number of teeth with untreated caries in primary or permanent teeth).

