All seven RCTs had a limited scope to dental screening, merely devoted to providing information to parents [7, 8]. No further attempts for follow-up communication and/or provision of assistance to parents with booking appointments was included [9–15]. A successful screening programme requires more than just the screening test; it should have a supporting system to ensure that those needing treatment are able to obtain it [6, 16, 17]. The provision of free dental services does not solve the problem as shown in the UK studies [9–11, 13, 15]. These extra efforts and costs to facilitate contact of screened-positive individuals with health services must be balanced against potential gains (clinical benefits) of the screening programme. Given the above reasons, it was not surprising that systematic reviews concluded that there is a need to conduct a well-designed trial with an intensive follow-up group [7, 8]. The present trial addresses these gaps in knowledge and methodological challenges.

The primary aim is to evaluate the effectiveness of two alternative approaches for school-based dental screening (referral to a specific treatment facility versus current practice —i.e. an information letter advising parents to take their child to a dentist—) in promoting dental attendance and reducing untreated caries among primary schoolchildren in Saudi Arabia. A secondary aim is to determine the effectiveness of school-based dental screening among population subgroups (two subgroups will be specifically considered, namely children who were screened positive and children who reported being regular attenders at baseline).

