### Trial interventions

Children in both groups will be examined for dental caries. The difference between the two trial groups lies in the referral mechanism. A comparison against no intervention was disregarded due to ethical concerns (children would be examined and not informed of their oral problems). Those having untreated dental caries according to the World Health Organisation (WHO) [20] criteria will be considered screened positive and referred according to their allocated group. All others will be considered screened-negative and will not receive a referral.

After dental examinations, screened-positive children in the intervention group will be referred to a specific hospital for treatment (referral to a specific treatment facility), King Saud University Dental College (KSU-DC). Referral to this specific institution is one of the innovations in the proposed research. The triage unit at KSU-DC will provide any urgent care needed and make an appointment for subsequent care. All treatments will be provided free of charge. Screened-positive children in the comparison group will receive the currently accepted practice for school-based dental screening; that is, a letter will be sent to parents informing them of the child’s dental problem and advising to take them to a dentist (conventional screening). For both groups, referral letters will be sent to parents through children’s school bags.

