### Data analysis

#### Justification of sample size

Based on a previous relevant study [15], a sample size of 910 children (455 in each trial group) is required to detect a 0.50-unit difference in the number of teeth with untreated caries between the conventional screening group and specific screening group, assuming 80% statistical power, 5% significance level and intra-class correlation coefficient (ICC) for dental caries at school level of 0.03. The total sample size will be rounded up to 1010 (505 in each group) to allow for a dropout rate of up to 11%. After compensating for the clustering of children within schools, there will be six clusters per group, each cluster will include at least 75 participants.

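### Planned subgroup comparisons answer effectiveness within a subgroup, but without an interaction estimate or results for irregular attenders they cannot support a statement that the effect differs by area or attendance

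*Protocol article*

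**What the plan says.** The Background sets the aim: "A secondary aim is to determine the effectiveness of school-based dental screening among population subgroups". It names two such groups: "two subgroups will be specifically considered, namely children who were screened positive and children who reported being regular attenders at baseline".

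The Supplemental analysis section gives the purpose, "Subgroup analysis will be conducted to explore the effectiveness of school-based dental screening on primary and secondary outcomes among specific subgroups", and the method: the two arms are compared "among children who were screened positive, and then, among those who reported being regular attenders at baseline". It then adds: "Comparisons will also be reported stratified by area (high and low socioeconomic status) and dentition".

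No interaction term is mentioned. Children who are not regular attenders appear in no planned subgroup comparison. For area, both levels are to be reported.

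The Trial interventions section says of children without untreated caries: "All others will be considered screened-negative and will not receive a referral".

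**The concern.** An arm comparison inside one subgroup estimates the effect in that subgroup. It does not measure how that effect compares with the effect elsewhere. Two features of the plan matter here.

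- **Area.** Results for high and low socioeconomic areas will stand side by side, and readers will compare them. One significant result and one non-significant result can easily arise from the same underlying effect.
- **Attendance.** Only regular attenders are analysed. Yet the Background and Discussion argue that screening may work in Saudi Arabia because visits without symptoms are uncommon. That rationale points to the children who are not regular attenders, and the plan gives no estimate for them. A null result in regular attenders alone would say little about whether attendance pattern matters.

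The Discussion says a positive result would support national implementation. A claim that referral works in only one kind of area could therefore carry weight that the data do not give it.

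**Working it through.** **Inputs from the protocol.** Justification of sample size: "a sample size of 910 children (455 in each trial group) is required to detect a 0.50-unit difference", with 80% power, 5% significance (two-sided assumed), ICC 0.03 and clusters of at least 75. Setting and participants: 16 schools. Trial design: 1:1 allocation.

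**Assumptions not in the protocol.** The SD; an equal split of schools, giving 4 per arm in each area; the share of regular attenders; and a normal approximation on school means in place of the planned negative binomial model.

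**Step 1: recover the SD from the plan's own figure.** Design effect = 1 + (75 − 1) × 0.03 = 3.22. Unclustered n per arm = 2 × (SD × 2.8016 / 0.50)². With SD = 1.5 this is 141.3, and 141.3 × 3.22 = 454.9, which matches 455. SD 1.25 gives 316 and SD 1.75 gives 619. The SD is therefore back-solved; this is not an independent check of the sample size.

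**Step 2: power inside one area.** Children per school = 910 / 16 = 56.9.

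SE = SD × √[(2/k) × (ICC + (1 − ICC)/m)], with k schools per arm and m children per school.

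For k = 4, m = 56.9 and SD 1.5: SE = 1.5 × √[0.5 × (0.03 + 0.97/56.9)] = 0.230. The standardised effect is 0.50 / 0.230 = 2.17. Against t with 6 df (critical value 2.447), power is 44.7%.

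**Step 3: discordant verdicts when both areas have the same effect.** The areas contain different schools, so the two results are independent. P(exactly one significant) = 2 × 0.447 × 0.553 = 49%.

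| SD | Power per area | Exactly one area significant |
|---|---|---|
| 1.25 | 58.8% | 48% |
| 1.5 | 44.7% | 49% |
| 1.75 | 34.8% | 45% |
| 2.0 | 28.0% | 40% |

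The sample-size section gives six clusters per group, not the eight that 16 schools imply. With 3 schools per arm per area, m = 910/12 = 75.8 and t with 4 df, power at SD 1.5 is 32.9% and discordance 2 × 0.329 × 0.671 = 44%. In that layout an SD of 2.0 lowers power to 20.9% and discordance to 33%.

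**Step 4: what an interaction estimate would offer.** Its type I error is 5% by construction when the effects are equal. Its SE for area is √2 × 0.230 = 0.325 teeth. Under the normal approximation, power for a 0.50-tooth difference between areas is about 34% (about 29% with six clusters per group). The 95% interval is about ±1.96 × 0.325 = ±0.64 teeth.

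**Step 5: regular attenders alone.** With 8 schools per arm, SD 1.5 and t with 14 df, power for an effect of 0.50 is 28%, 45% and 56% if they are 10%, 20% and 30% of children. These shares are assumptions. The Background says only that most Saudis attend when in pain, and non-Saudi children are also eligible.

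**The case against.** The strongest reply is that the protocol never says it will infer a difference. The aim and the analysis section both ask for effectiveness within named groups. An arm comparison with its estimate and interval answers that. The analyses are pre-specified, sit under a supplemental heading and are worded as exploratory. The Between-group comparisons section commits to absolute and relative effect measures, so the plan is not built on significance verdicts. All of this stands. A reader might infer that the plan will judge subgroup differences by contrasting p-values and so will often mislead; the text does not support that reading.

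Other parts of the reply also stand:

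- The screened-positive comparison is sound. Children who screen negative are referred in neither arm, so this analysis addresses the children who can receive the intervention.
- Area is not one of the two subgroups in the secondary aim, so the discordance figure does not bear on that aim.
- For attendance, only one side is analysed, so a significant-versus-not contrast cannot arise from the plan as written. The gap there is the missing estimate.
- Dentition splits the outcome, not the children, and is outside this point.

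An analysis plan that is not shown might add an interaction term. The protocol does state a method, however, and nothing in it points to such a term. Low interaction power is a reason for modest wording, not for leaving the estimate out.

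**Conclusion.** A minor point that holds in limited form. The planned comparisons meet the stated aim of effectiveness within a subgroup. They give no basis for saying that the effect differs by area or attendance pattern, and they leave children who are not regular attenders without an estimate.

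Under an identical effect of 0.50 teeth, the two area verdicts would disagree in roughly 40% to 50% of trials. This rests on SD 1.25 to 2.0 (unstated; 1.5 by back-solving), ICC 0.03, and 16 schools split equally between areas and arms. The figure matters only if someone contrasts the two area verdicts, which the protocol does not propose but side-by-side reporting invites. The primary conclusion is unaffected.

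**What to change.** For area and for attendance pattern, fit one model in all children, allowing for clustering by school, with an arm-by-subgroup term. Report the effect with its interval in both levels (high and low area; regular and not regular attenders), plus the interaction estimate with its interval. The plan already promises rate ratios and absolute differences, so state the scale on which the interaction is judged.

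State in advance that any claim of a differing effect rests on the interaction only, and that it is exploratory and low-powered. Keep the screened-positive analysis as planned.

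The cost is one extra model term per factor. No new data are needed: area is the stratification factor and attendance pattern is collected at baseline. The downside is imprecise interaction estimates, which should be presented as such.
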